#### Secondary Aims Analysis

We will explore whether hypothesized mediators at month 3 and month 6 mediate the relationship between intervention arm assignment and suicidal ideation and depressive distress at month 12. We hypothesize that factors targeted by the intervention—namely, family communication, family satisfaction, family acceptance, and community belonging—will mediate the effects of the intervention on the primary outcomes: past 3-month suicidal ideation and past 2-week depressive distress.

Causal mediation analysis methods [62,63] will be used to estimate the total, direct, and indirect effects of each mediator individually, followed by their combined joint effect [64]. We will also calculate the proportion mediated to determine the extent to which each mediator (or the set of mediators) accounts for the total effect of the intervention. These mediation analyses will be conducted using a series of random effects logistic regression models.

Additionally, we will explore differences in family characteristics based on whether a supportive caregiver could be identified and agreed to participate. These comparisons will offer valuable insights for refining future intervention strategies. TGD young adult-caregiver dyads also complete an additional measure to assess the impact of joint participation on the dyadic relationship. We will further examine potential differences in outcomes between linked and unlinked dyads.

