**Figure 1 figure1:**
[figure not shown]
TransHealthGUIDE (Transforming Mental Health for Transgender and Gender-Diverse Young Adults Using Interventions to Drive Equity) study schema. Target sample size is 500 TGD young adults, with one-quarter (125 participants) in a dyad with a caregiver (target sample size of 125 caregivers). TGD: transgender, nonbinary, and gender diverse.

Participants in the immediate intervention arm receive full access to the TransHealthGUIDE digital app for the first 6 months. This is followed by a 6-month observation period during which they retain access to the app but receive no new intervention content or engagement prompts. Participants in the deferred intervention arm receive limited access to the app for the first 6 months, consisting primarily of curated local, regional, and national support resources. At the 6-month mark, participants in the deferred arm are granted full access to the digital app for the remainder of their participation.

Survey assessments are administered at baseline, 6 months, and 12 months to evaluate primary outcomes (past 3-month suicidal ideation and past 2-week depressive distress) as well as secondary measures.

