### Intervention Delivery

TGD young adults and caregivers assigned to the immediate intervention arm receive full access to the digital app. After informed consent is obtained, participants are emailed a personalized link to download the app and complete registration. Only enrolled participants are able to create an account and access the app content. Participants randomized to the deferred arm also receive immediate access to the app; however, they are initially limited to viewing the Community Resources tab, which includes local, regional, and national resources. All other features are automatically unlocked after 6 months.

The intervention supports dyadic participation, with approximately one-third of TGD young adults expected to participate alongside a caregiver. With mutual consent, TGD young adults and caregivers may choose to link their accounts. All linking is reviewed and performed manually by study staff to ensure participant privacy and data integrity.

For dyads, accounts are manually linked by research staff once both participants have downloaded the app and completed registration. If linking is requested after enrollment, the app includes a feature that allows both participants to independently provide consent for linking. Once consent is confirmed, the study team is notified, and accounts are linked manually. Linking allows for shared activities and progress tracking but is entirely optional. Participants may request to unlink their accounts at any time, and study staff will promptly honor the request. This option, along with the voluntary nature of linking, is clearly communicated during the consent process and outlined in study documentation.

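### The mediation analysis uses month-12 outcomes, when the arm contrast is early versus delayed access to the full app, so its total effect, direct effect and proportion mediated do not describe the app's effect

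*Protocol article*

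**What the plan says.** The Secondary Aims Analysis section of the protocol article fixes the three parts of the mediation model.

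- **Exposure:** randomized arm.
- **Mediators:** "We will explore whether hypothesized mediators at month 3 and month 6". They are family communication, family satisfaction, family acceptance and community belonging.
- **Outcome:** the analysis asks whether these "mediate the relationship between intervention arm assignment and suicidal ideation and depressive distress at month 12".

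Causal mediation methods "will be used to estimate the total, direct, and indirect effects of each mediator individually", then jointly. The section adds: "We will also calculate the proportion mediated". That percentage is to be read as the share of the intervention's total effect that each mediator, or the set, explains.

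On access to the app, Study Design (below Figure 1) says: "At the 6-month mark, participants in the deferred arm are granted full access to the digital app for the remainder of their participation". Intervention Delivery confirms that this is automatic. Deferred participants start with the Community Resources tab only, and then: "All other features are automatically unlocked after 6 months". Over months 6 to 12 the immediate arm keeps access but gets no new content or prompts.

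**The concern.** The mediators are measured up to the moment of crossover and the outcome six months after it. Ideation at month 12 looks back three months and depressive distress two weeks, so both windows lie wholly after the deferred arm has the full app. The deferred arm's outcome therefore reflects an exposure that its mediator values do not.

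This has two consequences. First, the total effect between arms at month 12 is that of receiving the app early rather than late, which is not the quantity the section says it will decompose. Second, any benefit the deferred arm gains after month 6 bypasses the measured mediators. It is assigned to the direct effect and works against the indirect effect. The better the app works in the deferred arm, the smaller the denominator of the proportion mediated and the harder that percentage is to interpret.

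**Working it through.** **Timeline**

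| Period | Immediate arm | Deferred arm | What is measured |
|---|---|---|---|
| Months 0–6 | Full app | Resources tab only | Mediators (months 3 and 6) |
| Months 6–12 | Access kept, no new content or prompts | Full app | Outcome (month 12) |

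The other effectiveness analyses avoid the problem. The primary analysis stops at 6 months (Primary Aim Analyses), and the sustained-effect analysis uses the immediate arm alone (Supplemental Analyses). Only the mediation section compares arms after crossover, and it does not mention the crossover.

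**The plan's own figure**

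The Power section gives a risk ratio of 0.70, 200 per arm, 80% power and a 0.05 level. It states no control-arm risk, so 200 cannot be reproduced from its inputs alone. Solving backwards with the two-sided pooled formula for two proportions gives 203 per arm at a control risk of 0.45 and 196 at 0.46. I therefore assume 0.45. The attrition step reproduces: 400 / (1 − 0.20) = 500.

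**Erosion of the month-12 contrast**

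Assumptions: control risk 0.45, the immediate arm holding 0.70 × 0.45 = 0.315 to month 12, and the deferred arm gaining a fraction f of the effect after month 6. Then:

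- Deferred-arm risk p_D = 0.45 × (1 − 0.30f)
- Risk ratio = 0.315 / p_D
- d = p_D − 0.315, and p̄ is the mean of the two risks
- s₀ = √[2p̄(1 − p̄)/200]
- s₁ = √[p_D(1 − p_D)/200 + 0.315 × 0.685/200]
- Power = Φ[(d − 1.96s₀)/s₁] + Φ[(−d − 1.96s₀)/s₁]

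For f = 0.5: p_D = 0.3825, d = 0.0675, s₀ = 0.0477, s₁ = 0.0475. The first term is Φ(−0.545) = 0.29 and the second is negligible.

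| f | Deferred risk | Risk ratio | Power |
|---|---|---|---|
| 0 | 0.450 | 0.70 | 80% |
| 0.25 | 0.416 | 0.76 | 56% |
| 0.50 | 0.383 | 0.82 | 29% |
| 0.75 | 0.349 | 0.90 | 11% |
| 1.00 | 0.315 | 1.00 | 5% (false-positive rate) |

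**Sensitivity to the assumptions**

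- *Control risk:* at f = 0.5, power is about 19% for a control risk of 0.30 and 44% for 0.60. With no catch-up these are about 54% and 95%.
- *Scale:* if catch-up is proportional on the log-risk scale, power at 0.45 is 52%, 25% and 9% for f = 0.25, 0.5 and 0.75.
- *Waning:* if the deferred arm gains the whole effect and the immediate arm keeps half of its own on the log scale, the risk ratio reverses to 0.70^0.5 / 0.70 = 1.20.

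**Stability of the proportion mediated**

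Its denominator is the estimated total effect. In simulation at a control risk of 0.43, 200 per arm and log-scale catch-up, that estimate was zero or in the wrong direction in 0.4% of trials at f = 0, 12% at f = 0.5, 29% at f = 0.75 and 52% at f = 1.

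**What survives**

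A second simulation assumed a mediator shift of 0.5 SD, a log-odds slope of −1 per SD and an outcome driven wholly by the mediator. As f rose from 0 to 1, the total risk difference went from −0.096 to 0.00. The estimated indirect effect stayed between about −0.095 and −0.097, and the direct effect took the opposite sign.

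**The case against.** The strongest reply has four parts.

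1. **The indirect effect can survive.** The path from arm to mediator is measured before crossover and remains a randomized comparison of app with waitlist. Mediation methods do not need a significant total effect. This stands. A reader might infer that a real family-support pathway would show up as no mediation. The documents do not support that, and the second simulation shows the indirect effect intact under its assumed values.

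2. **The size of the loss is not known.** A reader might infer that the month-12 effect is largely erased by design. The article gives no deferred-arm uptake or response and no control-arm risk. At 25% catch-up, more than half the power remains. What can be said is that the effect is attenuated to an unknown degree.

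3. **The reporting scale is open.** The section says: "These mediation analyses will be conducted using a series of random effects logistic regression models". A reader might infer that effects will be reported as conditional odds ratios that cannot match the primary risk ratio. The text does not say so. Logistic fits can be averaged to marginal risks, and that detail is commonly left to an analysis plan. I make no point of it.

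4. **The analysis is exploratory, and a later outcome gives temporal order.** Both are true, and they lower the severity. They do not make the contrast the one that is named, because the order is gained by giving up the waitlist comparator.

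**Conclusion.** The point holds. The crossover at month 6 and the outcome at month 12 are both explicit, so the month-12 arm contrast is early versus delayed access. Carried out as written, the plan would give a total effect, a direct effect and a proportion mediated that are misleading or unstable as statements about the app. The indirect effect may still be detected.

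How much is lost depends on the deferred arm's response after month 6 and on the immediate arm's maintenance of its effect, neither of which the article gives. The figures above are therefore a range under assumptions. Only a negligible deferred-arm response would leave the contrast intact.

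Severity is moderate. This is an exploratory secondary-aim analysis, and neither the sample size nor the primary conclusion depends on it.

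**What to change.** - **Move the outcome.** Make the month-6 outcome, the last app-versus-waitlist comparison, the target of the mediation analysis, adjusting for baseline mediator and baseline outcome.
- **Settle the month-3 survey first.** Remuneration, Primary Aim Analyses and Secondary Aims Analysis presuppose it. Study Design and Self-Reported Surveys list only baseline, 6 and 12 months. If it is fielded, use month-3 mediators. If not, use month-6 mediators and state that temporal order is lost: the family measures and ideation would then share the same three-month recall window.
- **Relabel month 12.** Describe any month-12 arm contrast or decomposition as early versus delayed access, and report no proportion mediated from it.
- **Do not promise equality with the primary result.** A reader might expect the month-6 total effect to equal the primary risk ratio. The primary model has one arm term and a time term for months 3 and 6, so its estimate pools both visits and need not match.

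**Cost:** changes to wording in the protocol and analysis plan, plus the schedule reconciliation. The month-6 outcome is already collected. The downside is a shorter lag between mediator and outcome, or none if month-6 mediators must be used. With five participants enrolled at the article's cut-off, the change could still have been prespecified at that point.

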#### Attrition Analysis

Attrition will be monitored monthly using data visualization techniques to track trends over time. Key metrics will include total enrollment, representation of target subgroups (by race, ethnicity, and geographic region), and rates of loss to follow-up. Statistical analyses will be conducted to compare participants retained in the study versus those lost to follow-up, focusing on differences in baseline characteristics.

Patterns of missingness will be systematically examined, and baseline responses will be compared between participants with complete versus incomplete data. To address potential biases due to missing data, modern missing data techniques will be used, with an emphasis on multiple imputation methods [65]. Sensitivity analyses will be conducted to compare results from complete-case analyses with those using multiple imputation, allowing for an assessment of the potential bias introduced by missing data.

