### Statistical Analysis

#### Power

The study aims to enroll 500 TGD participants between the ages of 18 and 24 years, 125 caregivers, and one-quarter of the young adult sample in a TGD young adult-caregiver dyad. The primary outcome of interest is past 3-month suicidal ideation.

Power calculations determined the sample size needed to detect a significant difference in suicidal ideation between the immediate and deferred intervention arms. To detect an effect size of at least 30% (risk ratio=0.70) in the reduction of suicidal ideation from baseline to 6 months postrandomization, a total sample size of 400 participants (200 per arm) is required to achieve 80% power at a 0.05 significance level.

We selected a 30% effect size threshold based on the assumption that smaller differences would not be clinically meaningful for public health scale-up. To account for an estimated 20% attrition rate, we plan to enroll 500 TGD young adult participants and 125 caregivers at baseline, yielding an anticipated analyzable sample of 400 TGD young adult participants and 100 caregivers.

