#### Primary Aim Analyses

The primary outcome is suicidal ideation in the past 3 months, assessed using the 6-item C-SSRS. The C-SSRS demonstrates strong validity, with 100% sensitivity and 99.4% specificity for identifying aborted suicide attempts, and 100% sensitivity and specificity for classifying interrupted and actual suicide attempts, when compared to clinician-administered instruments [41]. The secondary outcome is depressive distress over the past 2 weeks, measured using the Patient Health Questionnaire-9, where a score of ≥10 indicates a positive screen for symptoms of clinically elevated depressive symptoms (88% sensitivity and 88% specificity for detecting major depression) [43].

Before analysis, data will be audited for quality and completeness. Descriptive statistics—including counts, percentages, means, medians, standard deviations, and ranges—will summarize baseline characteristics. Group differences at baseline will be assessed using *t* tests for continuous variables and chi-square tests for categorical variables. Variables that differ significantly between study arms may be included as covariates in subsequent models. All analyses will be conducted using SAS or R statistical software.

To evaluate intervention effectiveness, we will use an intention-to-treat approach. Poisson generalized estimating equations with a log link function will estimate the population-average (marginal) effect of the intervention on suicidal ideation from baseline to 6 months postrandomization [60]. An unstructured correlation structure will be used to account for within-subject correlations across repeated measures (baseline, 3 months, and 6 months).

The primary endpoint analysis will compare the proportion of participants reporting suicidal ideation in the past 3 months between the immediate and deferred (waitlist control) arms. The model will include a common intercept and fixed effects for the intervention arm (immediate vs deferred) and time point (3 vs 6 months). Baseline characteristics that differ significantly between groups and variables related to missingness will be included as covariates, if appropriate.

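### The stated complete-case versus multiple-imputation comparison can show bias explained by observed data, but not dropout that depends on unobserved month-6 outcomes, so agreement between the two is weaker evidence than the plan implies

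*Protocol article*

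**What the plan says.** All references are to the protocol article.

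- **Attrition Analysis, main approach:** "modern missing data techniques will be used, with an emphasis on multiple imputation methods". The missingness assumption is not named.
- **Attrition Analysis, sensitivity:** the planned sensitivity analyses will "compare results from complete-case analyses with those using multiple imputation, allowing for an assessment of the potential bias introduced by missing data". This is the only missing-data sensitivity comparison the article gives, and the second half of the sentence is its stated purpose.
- **Attrition Analysis, descriptive checks:** the team will "compare participants retained in the study versus those lost to follow-up, focusing on differences in baseline characteristics" and will compare baseline responses by completeness of data.
- **Primary Aim Analyses:** "variables related to missingness will be included as covariates, if appropriate".
- **Power:** "To account for an estimated 20% attrition rate", 500 young adults are enrolled to leave 400. The design effect is a risk ratio of 0.70 for suicidal ideation.

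**The concern.** Every check listed works from observed data: baseline comparisons, covariates related to missingness, and imputation from what was recorded. None addresses dropout that depends on the participant's own unrecorded month-6 state.

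That kind of dropout is plausible here. Participants are told their arm (Intervention Allocation and Randomization), and suicidality is self-reported (Results, Community Engagement and CAB Feedback). Under the Safety Planning and Response Protocol, suicidality and depression responses are reviewed within 24 hours and worrying answers lead to a psychiatrist's assessment. Participants are told of the response procedures at consent and again at every survey. It is an inference, but someone with current ideation who does not want that contact can avoid it by not answering.

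The article states a purpose for the comparison, so this is a matter of what the text claims. If the two analyses agree, a reader following the text would take missing-data bias to have been assessed, when an important form of it had not been examined.

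**Working it through.** **1. The plan's own figures.** 400/(1 - 0.20) = 500 young adults and 100/(1 - 0.20) = 125 caregivers; both reproduce. With 1:1 allocation that is 250 per arm, of whom 200 are observed and 50 missing.

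**2. An assumed control risk.** The article gives none. Solving the two-proportion sample size (two-sided 0.05, 80% power, risk ratio 0.70) needs 244 per arm at a control risk of 0.40, 203 at 0.45, 201 at 0.453 and 170 at 0.50. The planned 200 per arm therefore fits a control risk of about 0.45. Steps 3 and 4 use 0.453; step 5 uses 0.45.

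**3. What the planned comparison can detect.** Assume that half the participants have ideation at baseline. Control month-6 risk is 0.739 with baseline ideation and 0.167 without (average 0.453). With a true risk ratio of 0.70 the immediate-arm risks are 0.517 and 0.117 (average 0.317). Let immediate-arm dropout be 34% with baseline ideation and 8.5% without, and control dropout 20% throughout.

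- Complete-case immediate risk = (0.517 × 0.66 + 0.117 × 0.915)/(0.66 + 0.915) = 0.285; risk ratio 0.285/0.453 = 0.628.
- Imputation using arm and baseline ideation recovers 0.317/0.453 = 0.700.

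The gap exposes the bias. The planned comparison works for this kind of dropout.

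**4. What it cannot detect.** Keep control dropout at 20% unrelated to outcome. In the immediate arm let dropout total 20% but be k times as likely with month-6 ideation. For k = 2:

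- Dropout without ideation = 0.2/(0.3171 × 2 + 0.6829) = 0.152; with ideation, 0.304.
- Complete-case immediate risk = 0.3171 × 0.6963/0.80 = 0.276; risk ratio 0.276/0.453 = 0.609.
- Imputation within baseline strata: retained risks are 0.468 and 0.098, average 0.283; risk ratio 0.283/0.453 = 0.625.

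| k | True RR 0.70: complete-case | True RR 0.70: imputation | True RR 1.00: complete-case | True RR 1.00: imputation |
|---|---|---|---|---|
| 1.5 | 0.648 | 0.658 | 0.944 | 0.962 |
| 2 | 0.609 | 0.625 | 0.906 | 0.936 |
| 3 | 0.554 | 0.577 | 0.857 | 0.902 |

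Both estimates overstate benefit. At a true ratio of 0.70 they differ from each other by about 0.01 to 0.02, while imputation is 0.04 to 0.12 from the truth. With no true effect the two differ by about 0.02 to 0.05, and both still suggest benefit.

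**5. What an arm-specific shift would show.** Assume observed risks of 45% deferred and 31.5% immediate (risk ratio 0.70), 20% missing per arm, and deferred-arm dropouts held at 45%. Immediate-arm overall risk q = 0.8 × 0.315 + 0.2 × m, where m is the assumed dropout risk. The standard error of the log risk ratio is approximated from the 200 observed per arm: √[(1 - 0.45)/(200 × 0.45) + (1 - q)/(200q)].

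| m | q | RR | 95% CI |
|---|---|---|---|
| 31.5% (as observed) | 0.315 | 0.70 | 0.54-0.90 |
| 45% (deferred-arm rate) | 0.342 | 0.76 | 0.59-0.97 |
| 50% | 0.352 | 0.78 | 0.61-1.00 (upper limit 0.997) |
| 55% | 0.362 | 0.80 | 0.63-1.02 |
| 60% | 0.372 | 0.83 | 0.65-1.05 |

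The tipping point lies just above 50%.

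**The case against.** **A reader might infer that the comparison is worthless because both methods rest on the same assumption.** They do not. Complete-case analysis needs the stricter condition, and step 3 shows the comparison exposing a real bias (0.628 against 0.700). It should be kept.

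**A reader might infer that modest informative dropout would overturn a positive result.** The figures do not support that. Immediate-arm dropouts would have to exceed about 50% ideation against 31.5% observed, an odds ratio of about 2.2 and worse than the deferred arm, while deferred-arm dropouts stay at 45%. Imputing immediate-arm dropouts at the deferred-arm rate leaves the result significant. So does equally informative dropout in both arms: at an odds ratio of 2.2 the risk ratio is 0.72 (0.57-0.91), and at 3.3 it is 0.74 (0.59-0.92).

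**A reader might infer that the deferred arm stays in to unlock the app.** The Intervention Delivery section says that the features unlock automatically after 6 months, so this is a weak reason to expect unequal dropout. Survey payments also apply to all participants.

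**An analysis for outcome-dependent dropout may be in a statistical analysis plan that is not shown.** That is fair: its absence from a condensed article is not an error, and the article's wording on missing-data techniques is open enough to include one. Nor does the article say that agreement proves robustness. What stands is that it assigns to one named comparison a purpose that the comparison only partly serves.

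**Imputation could recover more than step 4 shows.** This is also fair. That calculation used only arm and baseline ideation; depression scores, self-injury and app use could narrow the bias. They cannot remove the part that depends on the unrecorded month-6 state once observed data are accounted for.

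**Conclusion.** The point holds in a limited form. The stated comparison assesses missing-data bias explained by observed data. It does not assess dropout that depends on unobserved month-6 ideation or depressive distress, and the two estimates can nearly agree while both are wrong (0.609 and 0.625 against a true 0.70). Agreement therefore supports less than the Attrition Analysis sentence suggests.

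The possible effect on the conclusion is moderate. For a result exactly at the design effect, significance is lost only once immediate-arm dropouts pass about 50% ideation with deferred-arm dropouts unchanged. The size rests on assumptions the article does not supply: control risk near 45%, baseline ideation of 50%, equal 20% attrition per arm, the dropout ratios, imputation in its standard form, and an approximate standard error. The direction does not depend on the exact rates: when immediate-arm dropout is likelier with ideation than observed data explain, and control dropout is unrelated to outcome, both methods overstate benefit.

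**What to change.** In Attrition Analysis:

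1. Keep the complete-case versus multiple-imputation comparison.
2. State that the imputation assumes missing at random, and limit the claim to bias explained by observed data.
3. Add delta-adjusted (pattern-mixture) multiple imputation for month-6 suicidal ideation and depressive distress. Vary the shift separately by arm over a prespecified grid, include a scenario that imputes immediate-arm dropouts from the deferred arm, and report the tipping point.

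If an unseen analysis plan already contains item 3, only item 2 and a cross-reference are needed.

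The cost is a little more analysis code and one table, with no new data collection. It should be fixed before unblinding. The downside is that conclusions may look less firm.
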